### Inclusion criteria

Plaque psoriasis (primary indication for biologic).Treatment for at least 6 months with IL-23i or IL-17i in the standard dose (dose advised by the label).PASI ≤ 5 in the previous 6 months. If no PASI scores are available in the previous 6 months, it should be clear from the patient record that the psoriasis was clear or almost clear.PASI ≤ 5 at inclusion.DLQI ≤ 5 at inclusion.

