### Power and sample size analyses

The primary outcome is non-inferiority of persistent flares (PASI > 5 for ≥ 3 months) in the intervention group with a non-inferiority margin of 15%. If the upper limit of the 95% confidence interval of the difference in persistent flares between the intervention group versus control group exceeds 15% at 18 months of follow-up, it must be concluded that non-inferiority could not be demonstrated for DR [36]. A margin of 15% was chosen based on clinical grounds, and on previous DR studies [8, 37]. Inherent to the intervention, there could be a small increase in disease flares (i.e., loss of disease control) as drug dosages are lowered. However, it is expected, based on other studies [8, 35], that most flares will be easy to control in the end without residual damage for patients, for example by reintroduction of a higher dose or switch to another biologic. It is therefore expected that persistent flares will not occur very frequently, as has also been shown in the CONDOR trial [8]. In addition, in the UC arm, there will be disease flares as well, as PASI scores might fluctuate over time and some patients might experience loss of effectiveness of their biologic [38]. The chosen non-inferiority margin of 15% is to some extent arbitrary, but refers to a clinically acceptable difference in persistent flares. Of note, the point estimate should be much lower than the margin of 15%, because the margin refers to the upper limit of the 95% confidence interval of the difference in persistent flares which should not exceed 15%. Therefore, we found a margin of 15% (hence a point estimate << 15%) for the difference in persistent flares acceptable, especially because we know that effectiveness could often be regained in patients with persistent flares in studies on other biologics [8, 35]. With an expected chance of being able to reduce biologic dosages in > 50% of patients [8], the benefit-harm ratio seems well balanced by accepting this anticipated increase of persistent flares in patients undergoing DR compared to UC.

With this margin, one-sided testing (*α* = 0.025; 1 − β = 0.8) and a randomization ratio of 2:1 DR versus UC, we calculated that 222 patients need to be included to reject the null-hypothesis of inferiority. Taking a drop-out rate of 10% into account, 244 patients need to be included, with 162 in the DR arm and 82 in the UC arm.

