### Statistical analyses

All analysis will be done according to a per protocol analysis, as this is the preferred and most conservative analysis for non-inferiority studies [42]. Of note, all patients that follow the DR protocol (Fig. 1) will remain in the group they were allocated to, including DR patients that returned to their normal dose according to the protocol. Patients on a lower dose who should return to a higher dose according to the protocol are not included in per protocol analysis after the moment of protocol deviation. They will however complete the study procedures, and occurred protocol deviations will be summarized and reported. Subjects lost to follow-up will be included in analyses until their lost to follow-up date only. Information about patients lost to follow-up will be described. Intention-to-treat (ITT) analysis will be performed as well on all outcomes for sensitivity reasons, and as they are needed for the cost-effectiveness analysis. Data of patients who deviated from the protocol will be included in ITT analysis. For the ITT analyses, last observation carried forward (LOCF) will be used for imputation of missing data. The last available data from patients who are lost to follow-up will be imputed. Extent and nature of missing data will be described. Patient and treatment characteristics will be summarized as means or medians and percentages, depending on the type of measurement.

The primary outcome incidence proportion of persistent flares will be calculated for both groups. Number of patients with a persistent flare will be presented as proportions with corresponding confidence intervals. Confidence intervals of proportions will be calculated by Fishers exact tests (Clopper-Pearson), and the proportions will be compared using Fisher exact tests (open source calculator OpenEpi, V3.01) [43]. If the difference in incidence proportion of persistent flares in the intervention group versus the UC group exceeds the non-inferiority margin (15% difference in persistent flares) at 18 months of follow-up, it will be concluded that non-inferiority could not be demonstrated for DR. Time until the first persistent flare in both groups will be graphically presented by Kaplan-Meier survival estimation.

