The proportion of patients with successful DR will be expressed using descriptive statistics. PASI and DLQI course throughout the study will be compared between the intervention and control groups using mixed methods analysis. All disease-activity scores (PASI) will also be directly compared at each time point (every 3 months) between the two groups using an unpaired *t* test or a non-parametric alternative. PASI and DLQI at 12 and 18 months will be analyzed with ANCOVA in which the baseline values will be included as a covariate to gain efficiency. A multivariable regression analysis will be carried out in order to identify predictors for successful DR at month 12 and month 18. Possible candidate predictors will include baseline patient and treatment characteristics and baseline trough drug concentrations. Based on group size, we will test the four most promising variables. Proportions, rate ratios, and relative rate ratios, with corresponding confidence intervals, of SAEs and AEoSI will be described and differences between groups will be tested using classical statistical methods (Fisher exact test). SAEs and AEoSI *related to* DR will also be counted and expressed as proportions and rate ratios. A subanalysis for all outcomes will be made for the different drug classes and on individual drug level if appropriate (depending on numbers included per class).

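### The primary persistent-flare comparison is valid but unadjusted; standardising it for baseline PASI and biologic could narrow the deciding interval modestly at almost no cost

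*Protocol article*

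**What the plan says.** - **Primary comparison** (Protocol article, Statistical analyses): "the proportions will be compared using Fisher exact tests (open source calculator OpenEpi, V3.01". Clopper-Pearson intervals are given for the single proportions. No covariate or stratification factor is named.
- **Decision rule** (Power and sample size analyses): the trial is designed to test "non-inferiority of persistent flares (PASI > 5 for ≥ 3 months) in the intervention group with a non-inferiority margin of 15" percent, and the conclusion turns on the upper 95% limit of the difference.
- **Adjusted secondary analyses** (Statistical analyses): PASI and DLQI at months 12 and 18 are analysed by "ANCOVA in which the baseline values will be included as a covariate to gain efficiency".
- **Unadjusted secondary analyses** (same section): the visit-by-visit PASI comparisons use an unpaired t test or a non-parametric test.
- **Entry and randomisation**: Inclusion criteria require "PASI ≤ 5 at inclusion", and also PASI at or below 5 over the previous 6 months or a record of clear or almost clear skin. Randomisation is stratified by biologic only.

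**The concern.** The primary event is a threshold crossing on the PASI scale, and every patient enters at or below that threshold. Baseline PASI is therefore each patient's starting distance from the event and a natural prognostic covariate. The plan measures it and uses it for efficiency in two secondary ANCOVAs, but not in the comparison that decides non-inferiority.

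What is at stake is precision. If baseline PASI predicts persistent flare, adjustment narrows the interval whose upper limit is held against 15 points. That raises the chance of demonstrating non-inferiority when it is true, with no extra patients.

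**Working it through.** **Inputs from the article.** "one-sided testing (*α* = 0.025; 1 − β = 0.8) and a randomization ratio of 2:1 DR versus UC"; margin 15 points; "we calculated that 222 patients need to be included to reject the null-hypothesis of inferiority", which is 148 DR and 74 UC at 2:1; "Taking a drop-out rate of 10% into account, 244 patients need to be included".

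**Not in the article.** The flare rate is described only in words ("It is therefore expected that persistent flares will not occur very frequently"), and no association between baseline PASI and flare is given. Both are assumed below.

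**1. The plan's sample size.** With no stated rate, 222 cannot be reproduced forwards. Solving backwards with equal rates and z = 1.960 + 0.842 = 2.802:

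p(1 − p) = (0.15/2.802)² / (1/148 + 1/74) = 0.141, so p ≈ 0.17.

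At 17% in both arms the formula returns 74 + 148 = 222. The solution is not unique: 5% UC against 10% DR gives 219. For dropout, 222 × 1.10 = 244.2, matching 244.

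**2. Unadjusted precision at 17%.** SE = √[0.17 × 0.83 × (1/148 + 1/74)] = 0.0535. The 95% half-width is 1.96 × 0.0535 = 10.48 points. Power = Φ(0.15/0.0535 − 1.96) = 80.1%.

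**3. Effect of adjustment.** In large samples the SE is multiplied by √(1 − ρ²), where ρ² is the share of outcome variance explained by baseline PASI. Power becomes Φ(0.15/(SE√(1 − ρ²)) − 1.96).

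| ρ | Gain in power (points) |
|---|---|
| 0.2 | 1.6 |
| 0.3 | 3.6 |
| 0.4 | 6.4 |
| 0.5 | 9.9 |

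A gain of 5 points needs ρ of about 0.355. The question is which ρ is plausible.

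**4. Plausible ρ, first route.** Assume baseline PASI skewed within 0 to 5 (mean 1.5, SD 1.15) and a logistic effect per PASI point.

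| Flare rate, both arms | Odds ratio per point | R² | Half-width (points) | Power |
|---|---|---|---|---|
| 17% | 1.0 | 0 | 10.48 | 80.1% |
| 17% | 1.2 | 0.007 | 10.45 | 80.4% |
| 17% | 1.5 | 0.038 | 10.28 | 81.6% |
| 17% | 2.0 | 0.115 | 9.86 | 84.7% |
| 5% | 1.0 | 0 | 6.08 | 99.8% |
| 5% | 2.0 | 0.054 | 5.91 | 99.9% |

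The interval is 0% to 6.0% narrower at 17% and at most 2.7% narrower at 5%. In 4000 simulated trials per scenario, the ratio of adjusted to unadjusted SD was 1.00, 1.00, 0.98 and 0.94 at 17% for the four odds ratios, and 0.98 at 5% with odds ratio 2.0.

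For 5% UC against 10% DR, SE = √(0.10 × 0.90/148 + 0.05 × 0.95/74) = 0.0354 and power = Φ(0.10/0.0354 − 1.96) = 80.7%. With R² of 0.054 to 0.088 (the odds-ratio-2.0 values at 5% and 10%), the gain is 2.1 to 3.4 points.

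**5. Plausible ρ, second route.** Assume normal log PASI (SD 1, random intercept), baseline PASI at or below 5, a persistent flare as two consecutive values above 5 among six follow-up visits, and a 17% rate. The third and fourth columns add the 6-month entry criterion as two earlier visits at or below 5.

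| Visit-to-visit correlation | ρ, baseline criterion only | Gain (points) | ρ, with 6-month criterion | Gain (points) |
|---|---|---|---|---|
| 0.4 | 0.25 | 2.4 | 0.20 | 1.6 |
| 0.6 | 0.34 | 4.7 | 0.26 | 2.6 |
| 0.8 | 0.44 | 7.8 | 0.31 | 3.7 |

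Gains use unrounded ρ. The model has no arm effect and no response to the treatment changes that follow a flare, which would probably weaken the link further.

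**The case against.** A crude difference in proportions is unbiased under randomisation and is on the scale of the 15-point margin. Using ANCOVA for a continuous score creates no duty to adjust an infrequent binary outcome. All of this stands.

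A reader might infer more than the documents support in four ways:

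- **That the plan contradicts itself.** It does not. Its use of baseline PASI is mixed, since the visit-by-visit PASI tests are also unadjusted.
- **That chance imbalance near the threshold is a separate threat.** It is not. The crude 95% interval already covers that variation; adjustment removes part of it.
- **That the interval is shown to be too wide.** The article does not say how strongly baseline PASI predicts persistent flare, and eligibility restricts its range. The loss could be nil.
- **That the gain is 10 points or more.** That needs ρ of about 0.5, which neither route in the working reaches.

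The objection does not remove the asymmetry of cost and benefit: the covariate is already collected, and a standardised risk difference keeps both estimand and margin.

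**Conclusion.** The point holds as a missed efficiency gain, not as an error. The primary comparison is valid, and its interval may be wider than it needs to be.

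At about 17% flares in both arms, the gain over 80% power is roughly 0 to 5 points. It reaches about 8 only under a visit-to-visit correlation of 0.8 with the 6-month PASI criterion ignored. It is essentially nil if flares are near 5% in both arms, where power already exceeds 99%. The flare rate, the baseline PASI distribution and the prognostic strength are all assumptions. This is an optional, cheap improvement.

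**What to change.** In Statistical analyses, before any outcome data by arm are examined:

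- Make the primary estimate the marginal risk difference (DR minus UC) standardised from a logistic model with arm, continuous baseline PASI and the stratification factor (biologic, or drug class if cells are sparse).
- Give it a two-sided 95% confidence interval (robust or bootstrap) and compare the upper limit with 15%. A Fisher test addresses equality of proportions, so the sentence needs an interval for the difference in any case.
- Use a penalised fit if flares are few.
- Keep the crude risk difference, with its own interval, as a sensitivity analysis.

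The cost is a change of wording and standard software in place of the online calculator. No new data, visits or patients are needed, and the margin is unchanged. The downside is a small reliance on model fitting when events are few.

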**Table 2 Tab2:**
[figure not shown]
Schedule of enrolment, interventions, and assessments by study time point

*Abbreviations*: *M* months, *PASI* Psoriasis Area and Severity Index, *DLQI* Dermatology Life Quality Index, *EQ-5D-5L* European Quality of Life-5 Dimensions-5 Level questionnaire, *SF-36* Short Form-36 questionnaire, *iMTA MCQ* institute for Medical Technology Assessment Medical Consumption Questionnaire, *PCQ* Productivity Cost Questionnaire

Our primary outcome is non-inferiority of the incidence proportion of persistent flares (PASI > 5 for ≥ 3 months) in the intervention group. If the 95% confidence interval from the difference in incidence of persistent flares in the intervention group versus control group exceeds the non-inferiority margin (15% difference in persistent flares) at 18 months of follow-up, it can be concluded that non-inferiority could not be demonstrated for DR.

Our secondary study outcomes are as follows:

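### The Statistical analyses section sets the 15% margin against the observed difference in persistent flares, not against the upper 95% confidence limit used in the sample-size section

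*Protocol article*

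**What the plan says.** The protocol article states the primary criterion in three places.

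- **Power and sample size analyses.** Non-inferiority is not demonstrated "If the upper limit of the 95% confidence interval of the difference in persistent flares between the intervention group versus control group exceeds 15" (per cent) at 18 months. The section then explains itself: "the margin refers to the upper limit of the 95% confidence interval of the difference in persistent flares which should not exceed 15" (per cent), so the point estimate has to lie well under the margin. The test is specified as "one-sided testing (*α* = 0.025; 1 − β = 0.8").
- **Procedures and outcome measures** (text after Table 2). Non-inferiority is not demonstrated "If the 95% confidence interval from the difference in incidence of persistent flares in the intervention group versus control group exceeds the non-inferiority margin" of 15%.
- **Statistical analyses.** Non-inferiority is not demonstrated "If the difference in incidence proportion of persistent flares in the intervention group versus the UC group exceeds the non-inferiority margin" of 15% at 18 months. The methods named for the primary outcome are: "Confidence intervals of proportions will be calculated by Fishers exact tests (Clopper-Pearson), and the proportions will be compared using Fisher exact tests".

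**The concern.** The first two statements work with the confidence interval of the difference. The third, in the section that describes the analysis, works with the difference itself.

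Nothing else in that section fills the gap. A Clopper-Pearson interval describes one arm's proportion. A Fisher exact test of two proportions addresses the hypothesis that they are equal, not the hypothesis that DR is at least 15 points worse. Someone working from that section alone would have two single-arm intervals, a test of equality and a threshold for the observed difference, but no interval to compare with 15%.

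At stake is the trial's main conclusion. A result can meet the threshold in one section and fail the criterion in another, and it would be open to dispute afterwards which one governed.

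**Working it through.** **Inputs from the document.** Margin 15 percentage points; one-sided alpha 0.025; power 0.80; allocation 2:1; 222 patients before dropout, which at 2:1 is 148 DR and 74 UC; 244 patients after a 10% allowance (162 DR, 82 UC).

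**Assumed input.** The article gives no expected flare rates, so the UC rate is scanned from 1% to 30%.

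**1. The plan's own figure.** With p the same in both arms, the usual formula is

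n(UC) = (1.960 + 0.842)² × p(1 − p) × (1 + 1/2) / 0.15².

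At p = 0.17: 7.849 × 0.1411 × 1.5 / 0.0225 = 73.8, so 74 UC + 148 DR = 222. A 14% UC rate with 15% under DR also gives 222. The figure can therefore be reached under an upper-limit criterion, but the rates used are not stated, so it cannot be confirmed. The final number is 222 × 1.10 = 244.2, or 244.

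**2. False-claim rate at the margin.** Take X(DR) ~ Bin(n1, p + 0.15) and X(UC) ~ Bin(n0, p), and sum the exact probabilities of all outcomes that pass each rule.

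- Rule A: pass if X(DR)/n1 − X(UC)/n0 ≤ 0.15.
- Rule B: pass if the upper limit of the two-sided 95% Newcombe interval is below 0.15.

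| UC rate | A, 148/74 | B, 148/74 | A, 162/82 | B, 162/82 |
|---|---|---|---|---|
| 1% | 53.0% | 2.5% | 52.2% | 2.3% |
| 5% | 51.6% | 2.8% | 51.6% | 3.0% |
| 10% | 51.2% | 2.8% | 51.5% | 3.0% |
| 20% | 50.9% | 2.9% | 48.1% | 2.8% |
| 30% | 50.9% | 2.7% | 48.9% | 2.8% |

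Over the whole scan, rule A passes 51-53% of the time with 148/74 and 48-52% with 162/82. Rule B passes 2.3-3.1%.

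**3. Beyond the margin.** At a true 20-point excess and UC rates of 5-20%, rule A passes 12-22% of the time and rule B 0.1-0.3%.

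**4. Results on which the rules part.** With 148/74 and a simple Wald limit, the largest observed difference d that passes rule B solves d + 1.96 × √[p1(1 − p1)/148 + p0(1 − p0)/74] = 0.15, with p1 = p0 + d. At an observed UC rate of 5% this is 7.7 points: 0.0769 + 1.96 × √(0.000749 + 0.000642) = 0.150. It is 6.0 points at 10%, 4.7 at 15% and 3.6 at 20%. Observed differences between these values and 15 points fail rule B and pass rule A.

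**5. Illustration (hypothetical counts).** DR 36/148 = 24.3% and UC 7/74 = 9.5%, a difference of 14.9 points, which does not exceed 15. The Wilson upper limit for DR is 31.8% and the Wilson lower limit for UC is 4.7%. The Newcombe upper limit is 14.9 + √[(31.8 − 24.3)² + (9.5 − 4.7)²] = 23.8 points, well above the margin. The Fisher exact test gives p = 0.011, with DR worse.

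**The case against.** The best defence is that the Statistical analyses sentence says only when non-inferiority is not shown. An observed difference above 15 points always has an upper limit above 15 points, so taken literally the sentence is compatible with the upper-limit rule. It never says that a smaller observed difference is enough. The sample-size section also rules out a point-estimate reading in plain terms, and it ties the word margin to the upper limit. Finally, the article condenses a longer protocol, which may govern the analysis.

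Much of this stands. It makes a drafting slip the likely explanation, and it makes the error rate conditional on how the sentence is used. It does not remove the point. The other two sections state their criterion in the same negative form, so the parallel reading is that anything not exceeding 15% passes, and the Statistical analyses section offers no other criterion for success. This is also not a matter of omitted detail: the section states a criterion, and it differs from the one stated elsewhere.

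A reader might infer three stronger points, none of which the document supports:

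- **That the trial will run at a 50% false-claim rate.** This needs the sentence to be the full rule and the true excess to equal the margin. Step 3 shows the rate falling beyond it.
- **That there are three conflicting rules.** The wording under Procedures and outcome measures is loose, but an interval that exceeds the margin is naturally one that extends past it. That agrees with the sample-size section.
- **That the 222 patients show which rule was intended.** Without flare rates that match cannot be checked. The stated alpha of 0.025 does support the upper-limit rule.

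**Conclusion.** The Statistical analyses section mis-states the primary non-inferiority criterion and is inconsistent with the sample-size section. It also names no interval for the difference that could be compared with 15%.

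Used as the complete decision rule, it would pass a strategy whose true excess equals the margin about half the time, against roughly 2.5-3% under the upper-limit rule. The result rests on two independent binomial samples of the planned sizes and on UC flare rates between 1% and 30%. It hardly depends on the unstated rates. The intended rule can be recovered from the sample-size section, so this is a correction of the text and not a flaw in the design. Because it concerns the primary conclusion and sits in the analysis section, it should be made before the data are analysed.

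**What to change.** - **Statistical analyses:** replace the criterion with: *Non-inferiority is concluded only if the upper limit of the two-sided 95% confidence interval for the risk difference (DR minus UC) at 18 months is below 15 percentage points; otherwise it is not demonstrated.*
- **Same section:** name the interval method for the risk difference, for example Newcombe or Farrington-Manning, as the basis for the decision. The single-arm Clopper-Pearson intervals and the Fisher test can stay as description. In the check above Newcombe ran slightly over nominal in places (up to 3.1%), which is worth knowing when choosing.
- **Procedures and outcome measures:** refer to the upper limit of the 95% confidence interval where the text now refers to the interval.

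The cost is a few sentences of wording. No data collection, sample size or clinical procedure changes.

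### Successful dose reduction is led by a per-protocol analysis that removes patients who flare and stay on the reduced dose, so the success proportion is likely inflated

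*Protocol article*

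**What the plan says.** Under Secondary objectives, Procedures and outcome measures, and Definition of disease flare, successful DR is a dose below the standard dose together with PASI ≤ 5. The first two set it at months 12 and 18. The Statistical analyses section deals with it in one sentence: "The proportion of patients with successful DR will be expressed using descriptive statistics". A regression for predictors of successful DR at the same two time points follows.

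The analysis set comes from the opening of that section: "All analysis will be done according to a per protocol analysis, as this is the preferred and most conservative analysis for non-inferiority studies". Patients on a lower dose who should have gone back to a higher one "are not included in per protocol analysis after the moment of protocol deviation". For leavers the rule is: "Subjects lost to follow-up will be included in analyses until their lost to follow-up date only". DR patients who follow the strategy stay in their group, "including DR patients that returned to their normal dose according to the protocol".

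The same paragraph plans a second analysis: "Intention-to-treat (ITT) analysis will be performed as well on all outcomes for sensitivity reasons". It includes the deviators, and "For the ITT analyses, last observation carried forward (LOCF) will be used for imputation of missing data".

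The Dose reduction group section sets the trigger for return: PASI > 5 and/or DLQI > 10, or the patient's unwillingness to continue on the lower dose.

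**The concern.** A DR patient on a reduced dose with PASI > 5 fails the success definition. If that patient steps back as the protocol directs, they remain in the analysis as a non-success. If they stay on the reduced dose, the same flare leads to their removal from the denominator. Whether a failure is counted therefore depends on what happened after it. The data are not lost: the section says that these patients complete the study procedures, so observed outcomes are set aside.

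For a between-arm non-inferiority comparison, per protocol is commonly defended as guarding against dilution of a difference, and that is the article's stated reason. A descriptive proportion in one arm has no difference to dilute. There, removing patients who tend to be failures favours the strategy.

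This figure is the trial's measure of benefit. The Introduction states the aim as the number of patients who keep effectiveness and quality of life on a reduced dose. The Power and sample size analyses section sets an expected reduction in more than 50% of patients against the flare margin and concludes that "the benefit-harm ratio seems well balanced by accepting this anticipated increase of persistent flares in patients undergoing DR compared to UC". Readers will judge the results by the same balance. The predictor regression, if run on the same set, loses the same failures.

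**Working it through.** The article states no figure for this analysis, so there is none to reproduce. The calculation shows how far the denominator rule can move the result.

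**Inputs**
- DR arm: 162 patients (Power and sample size analyses).
- Base rate: 53%, the success figure the Introduction quotes from the previous trial, used only as an illustration. 162 × 0.53 ≈ 86, and 86/162 = 53.1%.
- Leavers: the planned 10% drop-out, 162 × 0.10 ≈ 16.
- Deviators (should step back, do not): no rate is given. Assumed 5%, 10% and 15%, that is 8, 16 and 24 patients.

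**Step 1. Deviators only, all of them failures.** Proportion = 86 / (162 − deviators).
- 5%: 86/154 = 55.8% (+2.7 points)
- 10%: 86/146 = 58.9% (+5.8 points)
- 15%: 86/138 = 62.3% (+9.2 points)

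**Step 2. Some deviators meet the success definition.** Success uses PASI alone, so a deviator with DLQI > 10 but PASI ≤ 5, or whose PASI has come back to ≤ 5 on the lower dose, is a success at the visit. With 16 deviators and a share q of them successful, proportion = (86 − 16q)/146.
- q = 0: 58.9%
- q = 25%: 82/146 = 56.2%
- q = 53%: 53.1%, no bias
- q = 75%: 74/146 = 50.7%, bias reversed

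The inflation therefore requires deviators to succeed less often than the DR arm as a whole. That is the likely case, since flare is the main reason they were due to step back.

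**Step 3. Leavers only.** Removing 16 leavers gives:
- all non-successes: 86/146 = 58.9%
- about the same rate as the rest (8 successes): 78/146 = 53.4%
- all successes: 70/146 = 47.9%

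The direction depends on the leavers' true status, which is unknown.

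**Step 4. The planned ITT analysis with LOCF.** Deviators are back in. A leaver last seen on a reduced dose with PASI ≤ 5 is carried forward as a success. In the extreme case where none of the 16 leavers is truly successful but all were last seen in that state, the result is (86 + 16)/162 = 102/162 = 63.0%, against 53.1%.

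**The case against.** The strongest reply is that a full-denominator analysis is already planned. ITT covers all outcomes and includes deviators, and the article promises to report deviations and describe losses. This stands, and a reader should not infer that no such figure will exist. What remains is that the ITT result is labelled a sensitivity analysis, so the per-protocol figure leads, and that LOCF can credit success to patients not seen at month 12 or 18.

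The removed group is also narrow. Patients who step back as directed stay in as non-successes. Exclusion begins only after the deviation, so a patient whose PASI > 5 is first found at the month-12 or month-18 visit still counts as a failure there. Only patients who met the trigger earlier and stayed on the lower dose disappear. This limits the size but not the direction of the incentive.

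Three stronger readings are tempting and are not supported:
- That dropping leavers also inflates the rate. This holds only if leavers are mostly non-successes, and the article does not say so. Combining 10% leavers and 10% deviators to reach 86/130 = 66.2% assumes that every one of them failed. If the leavers resembled the rest, the figure would be 78/130 = 60.0%.
- That every deviator is a failure. The PASI-only definition of success rules this out.
- That the result could not be compared with the 53% of the previous trial. The article does not state the analysis set behind that figure.

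Finally, this is a secondary, descriptive outcome, and counting leavers as non-successes is one convention among several. Both are fair. The second matters most in the predictor regression, where that coding would mix predictors of leaving with predictors of DR failure.

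**Conclusion.** The concern holds for deviators. The lead analysis of successful DR removes patients by a rule tied to the outcome, and the reason given for per protocol does not apply to a one-arm proportion. The reported rate is likely too high. Its size cannot be fixed from the article: about +3 to +9 points follows from an assumed 53% base rate, assumed deviation in 5% to 15% of the DR arm, and deviators who all fail. It shrinks as more deviators have PASI ≤ 5 at the visit.

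For leavers no direction can be claimed: with 10% lost, the per-protocol figure could lie anywhere from 47.9% to 58.9%. Neither planned analysis gives the proportion of all patients randomised to DR who are shown to be successful at the visit. The primary non-inferiority comparison is not touched by this point. The change is worth making before analysis.

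**What to change.** Add a short statement to the Statistical analyses section, for this outcome only:
- The lead denominator for successful DR at months 12 and 18 is all patients randomised to DR.
- Deviators are kept and classified by their observed dose and PASI at the visit.
- Leavers are counted in the lead proportion as not shown to be successful. The LOCF and per-protocol proportions are given as sensitivity analyses.
- In the predictor regression, deviators are likewise kept at their observed status. How leavers are handled there should be stated separately.

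No new data are needed, since deviators complete the study procedures. The cost is a somewhat less favourable success rate, which may be conservative if some patients left while doing well. The sensitivity analyses would show how much this matters.
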